#### Physiome Measurements

##### Blue Food Dye

At each baseline and postintervention clinic visit, participants ingested 1 teaspoon of Royal Blue Liqua-Gel (Chefmaster) food coloring (12 drops per 1.5 grams) in water. The intake time and date were recorded. The dye was poorly absorbed or fermented, which allowed for analysis of whole-gut transit time upon passing through visual confirmation [88,89]. Visual confirmation was recorded by the participant on the daily bowel movement diary app.

##### Atmo Gas-Sensing Capsule

A subset of participants (n=15) completed an assessment of colonic gas profiling and whole-gut and regional transit time through the Atmo gas-sensing capsule. The capsule measures temperature; a range of gaseous fermentation by-products, including carbon dioxide and hydrogen; and an indication of oxygen level, capsule tumble, and antenna reflectometry [90,91]. The selected participants received a separate participant information sheet and completed a specific consent form before the transit assessment. The capsule was ingested at each phase of baseline and at the end of the postintervention clinic visits. These participants consumed a standardized cereal bar and an Atmo gas-sensing capsule (Atmo Biosciences).

The selected participants were fitted with a sling bag containing a transponder. It consists of a receiver and smartphone with a custom app that “listens” to the capsule ingested. These participants wore or kept the Atmo transponder close to them (approximately 1 m) until the exit of the capsule or for up to 5 days. They were also asked to enter additional daily bowel movement diary information into the Atmo transponder. The data were collected in real time on the smartphone app and transmitted to an Atmo cloud during the passage to allow for remote monitoring and troubleshooting. Once the participant confirmed the exit of the capsule, they returned the transponder to the research team. The diary data from the Atmo app were then synchronized to the Atmo cloud for review and analysis. Blinded and deidentified data synchronized to the Atmo cloud were assessed using specialized Atmo software by trained Atmo team members. The analysis included colonic gas profiling (hydrogen and carbon dioxide) and the determination of whole-gut and regional transit times.

##### Adverse Events

Although the study is considered low risk, all participants were provided with information about managing possible side effects. Participants were encouraged to contact their health care provider, followed by our research team, in the event of side effects. Participants were encouraged to record any symptoms and may withdraw if they experienced any side effects. Any participants experiencing harm directly due to their involvement in the study were withdrawn from the study immediately.

#### Sample Size

Sample size calculations were based on the GutFeelingKB cohort [92]. The percentage of relative abundance of a composite microbiome index (incorporating 15 operational taxonomic units as outlined in this section) was estimated to be 28.3% with an SD of 14%. The sample size needed was 60 participants in this crossover study to account for a 15% dropout rate. The crossover study had >80% power to detect a difference in the absolute increase in the relative abundance of approximately 6% as statistically significant (2-tailed α=.05). An increase of 6% compared with the baseline level of 28% equates to a relative increase of approximately 22%. The consumption of 3 (for female individuals) or 4 (for male individuals) slices of DRB-fortified bread per day for 28 days is thought to affect individual and combined groups of the microbial taxa making up the composite.

The composite microbiome index included genera from 5 phyla found in the gut microbiota of healthy human adults. This index included the *Prevotella* and *Barnesiella* genera and *Bacteroides ovatus* and *Bacteroides xylanisolvens* from the *Bacteriodetes* phylum; the *Roseburia*, *Anaerostipes*, *Blautia*, *Eubacterium*, *Ruminococcus*, *Faecalibacterium*, and *Lactobacillus* genera from the *Firmicutes* (*Bacillota*) phylum; the *Bifidobacterium* and *Eggerthella *genera from the *Actinobacteria* (*Actinomycetota*) phylum; the *Akkermansia* genera from the *Verrucomicrobiota* phylum; and the *Methanobrevibacter* genera from the *Euryarcheaota* phylum.

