#### Statistical Analysis Plan

This study was conducted as a superiority trial. The guidelines of the Committee for Proprietary Medicinal Products (now termed Committee for Medicinal Products for Human Use) require intention-to-treat analysis [93]. For a crossover design, the intention-to-treat analysis means that every enrolled participant who has consumed both the intervention and placebo bread is included despite dropout or noncompliance. All data from randomized participants who received at least one intervention dose and had at least one postintervention measurement will be analyzed.

The mean differences from the baseline of most outcomes will be compared between groups and referred to as a between-group comparison. For most outcomes, within-group analysis (after the intervention compared with baseline) will also be performed. For metabolome analyses, postintervention values (not the mean differences) will be compared within and between groups.

All statistical analyses will be performed using SPSS statistics (version 29; IBM Corp) or R (version 4.3.1) by blinded researchers under the guidance of an independent biostatistician.

Baseline characteristics will be presented using descriptive statistics. The mean and SD, or median and range, will be used to describe continuous variables. Frequencies or percentages will be used to describe categorical variables. The group effects (ie, the mean change from baseline between groups) will be assessed using (parametric) 2-tailed *t* tests and (nonparametric) Mann-Whitney or Kruskal-Wallis tests for symmetrically and asymmetrically distributed data. Categorical variables will be assessed using chi-square tests (or Fisher exact tests for small samples). A 2-tailed *P*<.05 is determined as statistically significant. A value of *P*≤.10 will be considered a trend for most variables except for the microbiome data.

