For the primary outcome, to determine the microbiome composite, the selected genera and species will be summed to give a composite relative abundance for each participant. Changes in the composite of the microbial taxa within and between groups will be assessed using the nonparametric Wilcoxon signed rank test. The statistical significance level is determined at *P*<.05, with a false discovery rate (FDR) of *P*<.10. A probable biological significance level (trend) is assumed at an unadjusted *P*≤.10. For other fecal microbiome measures, univariate and multivariate statistical analyses will be used to assess α- and β-diversity variations, individual relative abundance differences in taxa, and gene abundance differences between groups. Differences in α-diversity between baseline and the postintervention assessment and between groups after the intervention will be assessed using the nonparametric Wilcoxon signed rank test with continuity correction. The Benjamini-Hochberg method will be applied to control the FDR inherent in multiple-hypothesis testing for variables in the microbiome and metabolome analyses. The resulting adjusted *P* values will be computed to address the inflated type-I error rates associated with numerous comparisons. *P*<.05 and an FDR of *P*<.10 will be deemed significant, with a probable biological significant difference (trend) assumed at an unadjusted *P*≤.10.

Box plots will be created using *ggplot2* to compare groups for each Chao1 and Shannon Indexes. The permutational multivariate ANOVA and the analysis of dissimilarity functions will then be used to assess the statistical significance of microbial community composition between individuals. Analysis of dissimilarity uses permutation testing and provides statistical assessments and their significance using *F* tests based on the sequential sums of squares from the permutations to determine whether the observed differences in β-diversity are statistically meaningful. Microbial differential gene expression will be performed using quasi-likelihood *F* tests. This test provides stricter error rate control by accounting for the uncertainty in dispersion estimation. Genes with an absolute log fold change of >1.1 will be considered as differentially expressed.

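### The stated power of over 80% rests on a between-person SD of 14% and is not supported for the planned primary contrast, a difference of changes from two period baselines; at an assumed correlation of 0.5 it would be about 57–61%

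*Protocol article*

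**What the plan says.** The Sample Size section of the protocol article takes its inputs from outside the trial: "Sample size calculations were based on the GutFeelingKB cohort". The composite "was estimated to be 28.3% with an SD of 14"%. On size it says "The sample size needed was 60 participants in this crossover study to account for a 15% dropout rate". The power claim is "The crossover study had >80% power to detect a difference in the absolute increase in the relative abundance of approximately 6" percentage points, "as statistically significant (2-tailed α=.05"). The effect is also given in relative terms: "An increase of 6% compared with the baseline level of 28% equates to a relative increase of approximately 22"%. No within-person SD, SD of change, correlation or formula is given.

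The Statistical Analysis Plan section sets the contrast: "The mean differences from the baseline of most outcomes will be compared between groups". For the primary outcome, "Changes in the composite of the microbial taxa within and between groups will be assessed using the nonparametric Wilcoxon signed rank test". The same section reserves comparison of post-intervention values alone for the metabolome. The section on timing of assessments places a separate baseline before each intervention period. The Results section reports 56 participants in the analysis.

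**The concern.** A mean of 28.3% with an SD of 14% describes how the composite level varies between people. A crossover test depends on a different quantity, the SD of the within-person contrast. Here that contrast is the change on fortified bread minus the change on placebo bread. It carries the noise of two post-intervention samples and two baseline samples. Under equal correlations its variance is twice that of a simple post-versus-post difference.

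This is the article's only power statement for the primary outcome, and readers will use it to interpret a null result. If the true power for a 6-point difference is nearer 60% than 80%, such a result would be over-read as evidence of no effect. Subtracting each baseline may also cost precision that the collected data could keep.

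**Working it through.** **Inputs.** From Sample Size: SD 14, difference 6 points, two-sided alpha 0.05, 60 participants, 15% dropout, so 60 × 0.85 = 51 completers. From Results: 56 analysed. The within-person correlation ρ is not in the article; it is an assumption, varied below. Power is from the noncentral t distribution for a paired comparison, with noncentrality 6√n / SD_d, where SD_d is the SD of the within-person contrast.

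**Step 1: reproduce the stated figure.** Put SD_d = 14.
- n = 51: 85.1%. n = 56: 88.3%. n = 60: 90.4%.
- With the usual efficiency of 0.955 for the Wilcoxon signed rank test under normality, n = 51 gives 83%.
- A parallel-group reading does not reproduce it: 30 per arm gives 38%.

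So the stated power follows if 14 serves unchanged as the SD of the paired contrast.

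**Step 2: the SD of the planned contrast.** Write B1, P1, B2, P2 for baseline and post-intervention values in the two periods, each with SD 14 and a common correlation ρ.
- Difference of changes, (P1 − B1) − (P2 − B2): SD_d = 14√[4(1 − ρ)] = 28√(1 − ρ).
- Post values only, P1 − P2: SD_d = 14√[2(1 − ρ)].

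Setting each equal to 14 gives ρ = 0.75 for the difference of changes and ρ = 0.5 for post values only.

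**Step 3: power for a 6-point difference, n = 51 / n = 56.**

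| ρ (assumed) | SD_d, changes | Power, changes | SD_d, post only | Power, post only |
|---|---|---|---|---|
| 0.3 | 23.4 | 43% / 47% | 16.6 | 72% / 76% |
| 0.5 | 19.8 | 57% / 61% | 14.0 | 85% / 88% |
| 0.6 | 17.7 | 66% / 70% | 12.5 | 92% / 94% |
| 0.7 | 15.3 | 78% / 82% | 10.8 | 97% / 98% |
| 0.75 | 14.0 | 85% / 88% | 9.9 | 99% / 99% |
| 0.8 | 12.5 | 92% / 94% | 8.9 | >99% / >99% |

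For 80% power the difference of changes needs ρ of about 0.71 / 0.68; post values alone need about 0.43 / 0.37.

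**Step 4: detectable difference.** At ρ = 0.5 (SD_d = 19.8), the difference detectable with 80% power is 7.9 points at n = 51 and 7.5 at n = 56. Against 28.3 these are 28% and 27% relative, where the article states about 22%.

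**Step 5: unequal correlations.** If all between-period correlations are equal, the variance of the difference of changes is 4 × 14² × (1 − r_w), where r_w is the baseline-to-post correlation within a period. The between-period correlation cancels. As a further example, let correlation decay with time, 0.6 at 4 weeks and 0.6^(t/4) at t weeks, with samples at weeks 0, 4, 6 and 10. The SD of the difference of changes is then 19.0 and power is 60% / 64%. The post difference adjusted for the baseline difference has residual SD 14.3 and power 83% / 87%. The loss is therefore not peculiar to equal correlations.

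**The case against.** **The claim could be right as it stands.** The article never says that 14 was used as the SD of the contrast; that is an inference from reproducing the figure. An undisclosed correlation of about 0.7 or more would support the claim for the difference of changes. Participants serving as their own controls, which the article gives as the reason for the crossover, neither establishes nor rules out such a value. This stands: no arithmetic error is shown.

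**A reader might infer that power is 57–61% unless the correlation reaches 0.7.** The documents do not support that. Those figures hold at ρ = 0.5 only. Power rises continuously with ρ, and nothing in the article singles out 0.5.

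**An article may leave the correlation to a fuller document.** True of a bare omission. But this article prints an SD, an effect, a power and a contrast, and these agree only under a high correlation that it does not state.

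**The contrast is not fully settled.** The overview of fecal samples defines the primary outcome as a difference in relative abundance against placebo bread, without mentioning change. However, the Abstract, the wording of the power claim itself (a difference in the increase) and the primary-outcome test all point to changes from baseline.

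**A covariate model is a late preference and may add little.** Partly right. Under equal correlations the post difference and the baseline difference are uncorrelated, so the covariate adds nothing and the whole gain comes from not subtracting baseline. Recruitment has also ended, and the Dietary Intake section writes of the primary analysis and unblinding in the past tense. This limits how the remedy may be used.

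**Conclusion.** The concern holds in limited form: the power of over 80% is unsupported for the planned primary contrast. Taking 14 as the SD of that contrast amounts to assuming ρ = 0.75 under equal correlations, which the article neither states nor justifies. Over assumed ρ from 0.3 to 0.7, power runs from 43/47% to 78/82% for 51/56 participants.

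These figures assume equal variances, a common correlation, approximate normality, and the cohort SD of 14 carrying over to this trial. The sample is already fixed, and the validity of the estimate and test is not in question. What is affected is how a null primary result may be read, and how efficiently the collected data are used.

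**What to change.** 1. **Restate the power in Sample Size.** Give the SD of the contrast actually analysed and the correlation assumed, with its source. Show power over ρ from 0.3 to 0.8, and say that over 80% for a difference of changes needs ρ of about 0.7. The cost is a few sentences and a less favourable figure.

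2. **Analyse the within-participant post-intervention difference, fortified minus placebo bread, with the difference between the period baselines as covariate, instead of subtracting baselines.** Change scores are the special case of a coefficient fixed at 1, so in large samples the adjusted analysis is no less precise. The covariate itself helps when within-period correlation exceeds between-period correlation. The cost is one coefficient and no extra participants or samples.

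3. **Respect the timing.** If the primary analysis has been run or unblinded, keep the prespecified Wilcoxon signed rank test as primary and report the adjusted analysis beside it as a labelled sensitivity analysis. Switching the primary analysis at that stage would cost credibility.

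4. **Make any blinded check address the right quantity.** It should estimate the SD of the contrast, including the baseline-to-post correlation within a period. Correlating baseline 1 with baseline 2 is not enough, because that correlation can cancel out of the contrast's variance.

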#### Statistical Analysis Plan

This study was conducted as a superiority trial. The guidelines of the Committee for Proprietary Medicinal Products (now termed Committee for Medicinal Products for Human Use) require intention-to-treat analysis [93]. For a crossover design, the intention-to-treat analysis means that every enrolled participant who has consumed both the intervention and placebo bread is included despite dropout or noncompliance. All data from randomized participants who received at least one intervention dose and had at least one postintervention measurement will be analyzed.

The mean differences from the baseline of most outcomes will be compared between groups and referred to as a between-group comparison. For most outcomes, within-group analysis (after the intervention compared with baseline) will also be performed. For metabolome analyses, postintervention values (not the mean differences) will be compared within and between groups.

All statistical analyses will be performed using SPSS statistics (version 29; IBM Corp) or R (version 4.3.1) by blinded researchers under the guidance of an independent biostatistician.

Baseline characteristics will be presented using descriptive statistics. The mean and SD, or median and range, will be used to describe continuous variables. Frequencies or percentages will be used to describe categorical variables. The group effects (ie, the mean change from baseline between groups) will be assessed using (parametric) 2-tailed *t* tests and (nonparametric) Mann-Whitney or Kruskal-Wallis tests for symmetrically and asymmetrically distributed data. Categorical variables will be assessed using chi-square tests (or Fisher exact tests for small samples). A 2-tailed *P*<.05 is determined as statistically significant. A value of *P*≤.10 will be considered a trend for most variables except for the microbiome data.

For the primary outcome, to determine the microbiome composite, the selected genera and species will be summed to give a composite relative abundance for each participant. Changes in the composite of the microbial taxa within and between groups will be assessed using the nonparametric Wilcoxon signed rank test. The statistical significance level is determined at *P*<.05, with a false discovery rate (FDR) of *P*<.10. A probable biological significance level (trend) is assumed at an unadjusted *P*≤.10. For other fecal microbiome measures, univariate and multivariate statistical analyses will be used to assess α- and β-diversity variations, individual relative abundance differences in taxa, and gene abundance differences between groups. Differences in α-diversity between baseline and the postintervention assessment and between groups after the intervention will be assessed using the nonparametric Wilcoxon signed rank test with continuity correction. The Benjamini-Hochberg method will be applied to control the FDR inherent in multiple-hypothesis testing for variables in the microbiome and metabolome analyses. The resulting adjusted *P* values will be computed to address the inflated type-I error rates associated with numerous comparisons. *P*<.05 and an FDR of *P*<.10 will be deemed significant, with a probable biological significant difference (trend) assumed at an unadjusted *P*≤.10.

Box plots will be created using *ggplot2* to compare groups for each Chao1 and Shannon Indexes. The permutational multivariate ANOVA and the analysis of dissimilarity functions will then be used to assess the statistical significance of microbial community composition between individuals. Analysis of dissimilarity uses permutation testing and provides statistical assessments and their significance using *F* tests based on the sequential sums of squares from the permutations to determine whether the observed differences in β-diversity are statistically meaningful. Microbial differential gene expression will be performed using quasi-likelihood *F* tests. This test provides stricter error rate control by accounting for the uncertainty in dispersion estimation. Genes with an absolute log fold change of >1.1 will be considered as differentially expressed.

As mentioned previously, the comparisons will be between each group and baseline and between groups after the intervention for plasma or fecal metabolome measures. The partial least squares projection discriminant analysis (PLS-DA) model will be performed to identify metabolites using SIMCA (version 17; Umetrics). The PLS-DA models will be subject to 100-fold permutations to evaluate performance; the models will be validated using the predictive ability of the model (Q2) and the ANOVA testing of cross-validated predictive residuals (ANOVA testing of cross-validated predictive residuals) [94]. The most discriminating features will be selected for building PLS-DA models. These models will be again subjected to prediction accuracy and overfitting assessment by the corresponding tests (ANOVA testing of cross-validated predictive residuals) and comparison of the Q2 afterward. Features will be selected based on their variable importance in the projection score. Univariate statistical analysis and heat maps will be performed using MetaboAnalyst (version 5.0) [95]. The metabolite and lipid relative intensity differences between groups will be tested through *t* tests or Wilcoxon rank sum tests. The multiple testing corrections will be controlled using FDR correction [96].

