**Methods:**

This is a 2-armed, placebo-controlled, double-blinded, crossover randomized controlled trial. The study duration is 14 weeks: 2 weeks of lead-in, 4 weeks of intervention per phase, 2 weeks of washout, and 2 weeks of follow-up. Overall, 60 healthy adults with low DF intake (<18 g [female individuals] or <22 g [male individuals] per day) were recruited in Christchurch, New Zealand, between June and December 2022. Randomly assigned participants consumed 3 (female individuals) or 4 (male individuals) slices of DRB-fortified bread per day and then placebo bread, and vice versa. The DRB-fortified bread provided 8 g (female individuals) or 10.6 g (male individuals) of total DF, whereas the placebo (a matched commercial white toast bread) provided 2.7 g (female individuals) or 3.6 g (male individuals) of total DF. Before and after each intervention phase, participants provided fecal and blood samples to assess biological responses; completed a 3-day food diary to assess usual intakes and web-based questionnaires to assess gut comfort, general and mental well-being, daily bread intake, and bowel movement via an app; underwent anthropometry and blood pressure measurements; and drank blue food dye to assess whole-gut transit time. Additionally, 25% (15/60) of the participants ingested Atmo gas-sensing capsules to assess colonic gas fermentation profile and whole-gut and regional transit time. Mean differences from baseline will be compared between the DRB and placebo groups, as well as within groups (after the intervention vs baseline). For metabolome analyses, comparisons will be made within and between groups using postintervention values.

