### Removal and Withdrawal Criteria

Participation in this study was voluntary, and participants could withdraw at any time without explanation, as stated on the participant information sheet.

In case of the following occurrences, participants were withdrawn:

The participant requested withdrawal from the study. Participants could decide to end their involvement in the study for any reason and at any time during the study.The investigator decided to withdraw a participant from the study when considered necessary. Examples include (1) nonrespect of at least one of the selection criteria after inclusion, (2) noncompliance with the study protocol, and (3) gastroenteritis or antibiotic use.The participant reported allergic reactions or adverse effects from either intervention.

Regardless of eligibility or continuing participation, an electronic case report form (eCRF) record was generated for each participant. The eCRF was designed specifically for the needs of this study and was the data collection instrument for the study. Therefore, all data requested on the eCRF were recorded, and all missing data were explained. Each eCRF had a unique 5-digit identifier to link the participant who had completed the screening questionnaire to their own data in a deidentified manner. Collected deidentified data, such as laboratory information, demographic information, and obtained questionnaire data, were stored in a password-protected customized database.

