## Results

Recruitment of participants began on June 1, 2022, and was completed on December 15, 2022. The study was approved by the University of Otago Human Ethics Committee (Health) on May 23, 2022. Of the 66 individuals who completed the web-based preliminary screening questionnaire and attended an on-site screening, 6% (n=4) were excluded as they did not meet the inclusion criteria. Therefore, 62 participants were randomized. During the first intervention phase, 10% (6/62) of the participants dropped out, resulting in a total of 56 participants (n=33, 59% female; n=23, 41% male; n=41, 73% New Zealand European; n=1, 2% Māori) included in the analysis.

The mean age for the entire cohort is 40.4 (SD 13.4) years, and the mean BMI is 21.9 (SD 10.3) kg/m^2^. Due to the large dataset, data analysis for all outcomes was planned to be completed by the last quarter of 2024, with full results expected to be published in peer-reviewed journals by the end of 2024.

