## Discussion

### Anticipated Findings

The primary aim of this study is to determine the influence of DRB-fortified bread on the relative abundances of a composite of selected key genera and species of the gut microbiota that are relevant in DF degradation and metabolism in healthy adults with low DF intake as compared with placebo white toast bread. In addition, relative abundance or concentration of fecal or plasma biological markers of host and microbial interactions (microbial taxa, bile acids, and organic acid concentrations) alongside cardiovascular health, patient-reported outcomes, and physiome outcomes of the recruited healthy participants will be described. The findings of this study are anticipated to provide a better understanding of the habitual impact of DRB-fortified bread on the gut microbiome and all other assessed parameters in healthy individuals with low DF intake.

Preliminary analysis showed that, during the first intervention phase, 10% (6/62) of the participants dropped out, resulting in a total of 56 participants (n=41, 73% New Zealand European and n=1, 2% Māori) included in the intention-to-treat analysis. Due to the large dataset, data analysis and publication of full results are expected to be completed by the end of 2024.

This is the first human study to explore DRB-fortified bread as a dietary intervention. Therefore, it was decided to recruit a generally healthy population of male and female individuals with low DF intake before the commencement of the study. In addition, participants were given a daily dose of 3 to 4 slices of DRB-fortified or white toast bread, which could easily be added to the diet. The bread slices were provided in separate doses tailored to the nutrient requirements for female (3 slices) and male (4 slices) individuals. Consequently, these strategies to improve DF intake among low DF consumers were practical and could be implemented in real-life settings. Furthermore, participants were specifically asked about their regular bread consumption. Therefore, only individuals who consumed bread were included in the study, which may reduce the generalizability of the study results. Nonetheless, these risk management measures aimed to minimize dropout and enhance the cost-effectiveness of the study.

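### Two inclusion rules that cannot both govern the analysis, and an intention-to-treat label on 56 of 62 randomized participants

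*Protocol article*

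**What the plan says.** In the Protocol article, the Statistical Analysis Plan section states that intention-to-treat is required and explains that for a crossover it means "every enrolled participant who has consumed both the intervention and placebo bread is included despite dropout or noncompliance". The sentence after it reads: "All data from randomized participants who received at least one intervention dose and had at least one postintervention measurement will be analyzed". Only the first of the two carries the intention-to-treat label.

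The same section names the primary test, a Wilcoxon signed rank test on the composite, within and between groups. For the change from baseline in other outcomes it names t tests and Mann-Whitney or Kruskal-Wallis tests.

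The Results section gives the flow: "Therefore, 62 participants were randomized", and then "During the first intervention phase, 10% (6/62) of the participants dropped out, resulting in a total of 56 participants". The Discussion (Anticipated Findings) describes those 56 as "included in the intention-to-treat analysis".

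Removal and Withdrawal Criteria lists among the occasions for withdrawal: "The participant reported allergic reactions or adverse effects from either intervention". It also gives noncompliance, gastroenteritis and antibiotic use as examples of reasons for the investigator to withdraw someone. Adverse Events adds: "Any participants experiencing harm directly due to their involvement in the study were withdrawn from the study immediately".

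**The concern.** Having eaten the second bread is something that happens after randomization. A set that requires it is selected on a post-randomization event, and a reader who sees the words intention-to-treat will assume that no such selection took place.

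Three things are at stake.

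- **Who is analysed.** With two rules in force, the population can be settled after the data are seen. Blinding and Allocation Concealment permits unblinding once the primary analysis is done, so for secondary outcomes the choice could be made with the allocation known.
- **Consistency.** If each test admits whatever data it can handle, the primary and secondary results may describe different people without saying so.
- **Possible selection by bread.** The withdrawal rules include reactions to the bread. Leaving in the first phase could therefore depend on which bread came first, and gut comfort and well-being are among the secondary outcomes.

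**Working it through.** **1. The reported flow reproduces.** From Results: 66 screened on site − 4 excluded = 62 randomized; 62 − 6 = 56 analysed; 6/62 = 9.7% (printed as 10%); 56/62 = 90.3%.

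**2. Apply each rule to the six who left.**

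| Rule | Requirement | Status of the six | Size of set |
|---|---|---|---|
| First sentence | ate both breads | out: they left in the first phase, before the second bread | at most 56 |
| Second sentence | one dose and one postintervention measurement | in, for any who have such a measurement | 56 to 62 |

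The upper figure for the second rule depends on how many of the six gave a postintervention measurement, which the article does not report.

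**3. Which rule does each test apply?**

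- Signed rank, between breads: it ranks within-person differences, so a person with one period contributes nothing. In effect this is the first rule.
- Signed rank, within a bread (after against before): it needs one period only, so it can follow the second rule.
- Mann-Whitney, Kruskal-Wallis and unpaired t tests: they accept one-period data and can follow the second rule. The article does not say whether its t tests are paired.

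**4. Could the six have usable data?** Timing of Assessments puts the first postintervention visit at day 29, and Study Overview allows it up to 3 days early. Stool collection and the questionnaire links are tied to that visit. A participant who left before it has no postintervention composite, and if that is true of all six, both rules give 56 for the primary outcome. Bowel and bread diaries, however, ran daily throughout the study, and the Gastrointestinal Symptom Rating Scale is described as given before and during bread intake. The rules are therefore more likely to diverge for those outcomes.

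**5. Is this a power problem?** Inputs from Sample Size: difference 6 points, SD 14, two-sided α 0.05. The within-person correlation ρ is not given, so it is an assumption here. SD of the paired difference = 14 × √(2(1 − ρ)); power ≈ Φ(6√n / SD_diff − 1.96).

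| ρ (assumed) | SD_diff | n = 56 | n = 62 |
|---|---|---|---|
| 0.3 | 16.57 | 0.77 | 0.81 |
| 0.5 | 14.00 | 0.89 | 0.92 |
| 0.7 | 10.84 | 0.985 | 0.992 |

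Six people cost at most a few points of power. In addition, 56 exceeds the 60 × 0.85 = 51 evaluable participants that the planned 15% dropout implies. Power is not the issue.

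**6. How large could the selection effect be?** Both calculations are hypothetical.

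- Suppose the 56 show a mean effect of 6 points. If the other six would have shown 0, the mean over 62 is (56 × 6 + 6 × 0)/62 = 5.4. If they would have shown −6, it is (336 − 36)/62 = 4.8.
- Permuted blocks of 4 (Randomization), assuming one unstratified list, give 15 full blocks and 2 further people, so 30 to 32 per sequence. If all six came from one sequence, it lost 6/32 = 19% to 6/30 = 20%. The article gives no split.

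**The case against.** The strongest reply is that the conflict may have no numerical effect on the primary outcome (step 4). If none of the six reached the day-29 visit, both sentences select the same 56, and no model can recover a treatment contrast from people without a postintervention value. That stands, and it limits the claim: the rule and the label are wrong as written, but the primary result is not shown to be wrong.

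Several stronger readings are tempting and should be resisted.

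- *The six left because of the bread.* The withdrawal criteria are rules; the article gives no reasons for the six. Tables of dropouts by sequence and reason may sit in the flowchart, which is not shown, so their absence is not a fault.
- *There are two intention-to-treat definitions.* Only the first sentence carries that label. The second is an available-data rule placed beside it.
- *The 56 are completers.* The first rule keeps someone who starts the second bread and then leaves. No later dropout is reported, but nothing says that all 56 finished.
- *The second rule cannot be run with the stated tests.* That is true only of the paired between-bread comparison (step 3).
- *The count of 60 shows further exclusions.* The abstract reports "Overall, 60 healthy adults with low DF intake" as recruited, against 62 randomized in Results. That is a small reporting mismatch and says nothing about the analysis population.

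None of this removes the core. One sentence excludes people whom the next sentence includes, and a set that lacks 9.7% of those randomized is called intention-to-treat.

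**Conclusion.** The point holds in limited form. The Statistical Analysis Plan contains two inclusion rules that disagree about anyone with first-period data only. The named tests split between them: the primary between-bread test follows the first, while several tests for other outcomes can follow the second. The intention-to-treat label on 56 of 62 is incorrect, because six randomized participants are left out after randomization.

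The size is six people, 9.7% of those randomized. The effect on power is small at every correlation tried. Bias related to the first bread is possible under the withdrawal rules but is not demonstrated, since neither reasons nor sequences are reported. For the primary outcome the two rules may coincide at 56; for diary and symptom outcomes they are more likely to differ. The correction should be made before full results are reported, because the choice of population is otherwise open.

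**What to change.** - State one rule for all outcomes: all randomized participants, analysed by allocated sequence, with every available postintervention value. Say how many contribute no such value for each outcome.
- Use a method that can apply the rule, such as a mixed model with bread, period and sequence terms and a participant effect. It uses one-period data and also gives form to the Discussion's statement that sequence effects were accounted for. It assumes that dropout is explained by the observed data, and this should be stated.
- Rename the 56 as participants with data from both periods, after confirming that this describes them. Keep the planned signed rank test on that set as a sensitivity analysis, and stop calling it intention-to-treat.
- When results are reported, account for the six by first bread and reason. This is what would show whether the exclusion depended on the bread.
- Reconcile inclusion despite noncompliance, in the Statistical Analysis Plan, with noncompliance as a ground for withdrawal in Removal and Withdrawal Criteria.
- As a minor edit, align the abstract's 60 with the 62 in Results.

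The cost is wording plus one model, with no new data. The composite may need a transformation for the model. One-period data will add little precision to a within-person contrast, so the gain is a defined population and an accurate label, not a tighter estimate.
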